**Methods:**

A randomized controlled trial will be conducted nationally among young Australians (aged 17-24 years) who experience anxiety symptoms and drink alcohol at hazardous or harmful levels. Participants will be individually randomized on a 1:1 basis to receive the *Inroads* intervention or assessment plus alcohol guidelines. Participants randomized to the *Inroads* intervention will receive access to 5 Web-based cognitive behavioral therapy (CBT) modules and weekly therapist support via email and/or phone. The primary outcome assessment will be 8 weeks post baseline, with follow-up assessment 6 months post baseline to determine the sustainability of the intervention effects. Primary outcomes will be the total number of standard drinks consumed in the past month (assessed by the Timeline Follow-Back procedure), severity of alcohol-related harms (assessed by the Brief Young Adult Alcohol Consequences Questionnaire), and anxiety symptoms across multiple disorders (assessed by the Generalized Anxiety Disorder-7). Secondary outcomes will include alcohol outcome expectancies; functional impairment and quality of life; and symptoms of social anxiety, anxious arousal, and depression. Results will be analyzed by intention-to-treat using multilevel mixed effects analysis for repeated measures.

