### Aims

This study will evaluate the efficacy of the *Inroads* program—a brief, Web-based CBT intervention that combines 5 online skills-based modules with minimal psychologist support for young adults (aged 17-24 years) who experience both anxiety symptoms and hazardous or harmful alcohol use. The study will be an RCT comparing the *Inroads* program with a control condition who will receive assessment plus alcohol guidelines and information. The study will be the first to evaluate the benefits of an early intervention for young adults targeting hazardous alcohol use, anxiety symptoms, and the interconnections between these problems.

It is hypothesized that compared with the control condition, the *Inroads* intervention will achieve greater reductions in (1) alcohol use, including drinks per drinking day and frequency of binge drinking; (2) alcohol-related harms; and (3) anxiety symptoms at 8 weeks post baseline. To assess the sustainability of these effects, outcomes for both groups will be assessed again at 6 months post baseline. Furthermore, it is hypothesized that participants allocated to receive the *Inroads* program will report decreased coping-motivated drinking and positive alcohol expectancies and greater improvements from baseline to post intervention on secondary outcomes of stress, social anxiety and depression symptoms, overall functioning, and quality of life.

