#### Primary Outcomes

Due to the focus of the study on co-occurring anxiety and hazardous alcohol use, primary outcomes encompass measurement across both anxiety symptoms and alcohol-related problems. Primary outcomes for alcohol are consumption per drinking day, calculated from the total number of Australian standard drinks (10 g of alcohol) consumed in the past month and assessed by a computerized version of the Timeline Follow-Back (TLFB; [53,54]) procedure and alcohol-related harm as assessed by the Brief-Young Adult Alcohol Consequences Questionnaire (B-YAACQ; [55]). The TLFB is a widely used procedure that has been validated across a number of countries and among a variety of subpopulations, including young adults, and the self-report computerized version has demonstrated good reliability with test-retest correlations exceeding 0.85 (see review by Deady [56]). The B-YAACQ assesses 24 age-appropriate consequences of alcohol consumption in the past 30 days using a dichotomous (0 “no” or 1 “yes”) response format. Scores range from 0 to 24, with higher scores indicating more problems and negative consequences from drinking. Primary outcomes for anxiety will be assessed by the Generalized Anxiety Disorder-7 (GAD-7) [48], which is sensitive to symptoms across anxiety disorders and has been previously used to assess outcomes in trials of internet-delivered treatment for mixed anxiety samples [57]. The GAD-7 contains 7 items, ranging from 0 “not at all” to 3 “nearly every day.” Total scores range from 0 to 21, with scores of 5, 10, and 15 representing cut points for mild, moderate, and severe anxiety, respectively.

**Table 1 table1:** *Inroads* study timeline.

Assessments		Study period				
		Enrollment	Pre-allocation	Allocation	Post-allocation	
			t_1_ (baseline)		t_2_ (8 weeks)	t_3_ (6 months)

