#### Secondary Outcomes

Module completion, time spent, rate of completion, and number and duration of therapist contacts via email, chat, and phone will be recorded to measure treatment retention and dose. Frequency of binge drinking (past month consumption of ≥5 standard drinks on 1 occasion) will be calculated from alcohol consumption data collected using the TLFB procedure [53,54]. Symptoms specific to social anxiety will be assessed using the 12-item Social Phobia Scale and Social Interaction Anxiety Scale-short forms [58]. Items are scored on a 5-point Likert-type scale from 0 “Not at all characteristic or true of me” to 4 “Extremely characteristic or true of me.” Total scores range from 0 to 48, with higher scores indicating higher levels of social anxiety. Symptoms of anxious arousal and depression will be assessed using the 21-item anxiety and depression subscales of the Depression and Anxiety Stress Scale [59]. Items are rated on a 4-point scale (0-3), summed and doubled for each subscale. Subscale scores range from 0 to 42, with higher scores indicating greater severity of emotional symptoms. Overall, functional impairment and quality of life will be assessed by the Sheehan Disability Scale [60] *.* Participants rate the extent to which their work, social life/leisure activities, and home life/family responsibilities are impaired by their symptoms on a 10-point visual analog scale. Higher numbers indicate greater impairment. The 3 items may be summed into a single dimension of global functioning impairment that ranges from 0 “unimpaired” to 30 “highly impaired.” The 28-item Drinking Motives Questionnaire-Revised [61] will be used to assess alcohol use motives across 5 subscales: social, coping-anxiety, coping-depression, enhancement, or conformity. Each item is rated on a 5-point Likert scale ranging from 1 “almost never/never” to 5 “almost always/always.” Subscales are scored as the average across the items within a scale, which allows a direct comparison across subscales. Positive alcohol expectancies will be assessed by the 17-item alcohol tension-reduction expectancies scale [62]. Each item is scored from 0 “not at all important” to 3” very important,” with total scores ranging from 0 to 51. Higher scores indicate greater expectancies regarding the tension-reducing effects of alcohol.

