### Sample Size

Previous evaluations of brief, multisession, internet-delivered interventions for young adults have indicated an effect size at post intervention of between 0.68 and 0.99 for reduction in the number of drinks consumed [39,75], 0.56 for reduction in alcohol-related consequences [75], and 0.59 for reduction in anxiety symptoms [76]. Optimal Design software [77] was used to calculate the required sample size, taking into account the multilevel analysis with a nested repeated measures design. Using a conservative approach with intraclass correlation coefficient of .55 estimated based on our adult comorbidity trial [37], power calculations indicated a sample size of 90 (45 each group) would be required to detect a moderate effect size of 0.50 between the intervention and control group with power=0.8 and alpha=.05. To allow for data attrition at post assessment, estimated at 35% (n=32/90) [78], a total sample of 122 individuals will be recruited to the study.

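### The primary alcohol-use outcome is total past-month drinks in the Abstract but drinks per drinking day in the Methods, and the two can lead to different conclusions

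*Protocol article*

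**What the plan says.** Four places in the protocol article bear on the alcohol-use outcome.

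- **Abstract, Methods:** "Primary outcomes will be the total number of standard drinks consumed in the past month", measured by the Timeline Follow-Back (TLFB).
- **Methods, Primary Outcomes:** "Primary outcomes for alcohol are consumption per drinking day, calculated from the total number of Australian standard drinks (10 g of alcohol"), again from the TLFB over the past month. Alcohol-related harm (B-YAACQ) and anxiety (GAD-7) are the other primary outcomes, and the Abstract and Methods agree on those.
- **Introduction, Aims:** the first hypothesis, for 8 weeks, concerns "alcohol use, including drinks per drinking day and frequency of binge drinking".
- **Methods, Secondary Outcomes:** "Frequency of binge drinking (past month consumption of ≥5 standard drinks on 1 occasion) will be calculated from alcohol consumption data" from the TLFB, which places binge frequency among the secondary measures.

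The Sample Size section cites earlier effects of "between 0.68 and 0.99 for reduction in the number of drinks consumed" and gives neither a period nor a denominator for that count. Table 1 has the TLFB at baseline, 8 weeks and 6 months.

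**The concern.** The past-month total is frequency times quantity. Drinks per drinking day is quantity alone. An intervention that mainly reduces the number of drinking occasions moves the first and may leave the second where it was. That is a plausible route here, since the third module teaches ways to cut down or avoid drinking.

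The article therefore does not fix which result decides the alcohol-use hypothesis. Both variables can be computed from one TLFB record, and the Statistical Analysis section applies the .05 level to each analysis. If the two disagree at 8 weeks, a reader with only this article cannot tell which was meant to count, and the choice could be made after the results are known.

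**Working it through.** **1. Do the wordings reconcile?** Write T for past-month drinks and D for past-month drinking days. The Abstract's outcome is T. The Methods' outcome is T/D. Saying that T/D is calculated from T gives the numerator but does not make the two the same variable. No section says that one replaces the other.

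**2. Can they disagree?** The values below are illustrative; the article gives no drinking distribution.

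| Change in drinking | T before → after | T/D before → after |
|---|---|---|
| 12 days at 6 drinks → 6 days at 6 drinks | 72 → 36 (−50%) | 6 → 6 (0%) |
| 12 days at 6 drinks → 4 days at 6 drinks | 72 → 24 (−67%) | 6 → 6 (0%) |
| 12 days at 6 drinks → 2 days at 8 drinks | 72 → 16 (−78%) | 6 → 8 (+33%) |

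In the third row the two move in opposite directions.

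**3. Is the sample size affected?** Inputs from the Sample Size section: d = 0.50, ICC 0.55, power 0.80, alpha .05. Assumed: a two-sided test and three assessments.

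- Variance factor = (1 + 2 × 0.55)/3 = 0.70.
- n per arm = 2 × (1.96 + 0.842)² × 0.70 / 0.50² ≈ 44, so N = 88 by the normal approximation.
- The noncentral t version gives 45 per arm, N = 90, which is the stated figure.

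The effect size is standardised, so the calculation is the same for T and for T/D.

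**4. What happens with no drinking days?** T = 0, but T/D = 0/0 unless a convention supplies a value. To see what the convention can do, assume that drinkers in both arms average 6 per drinking day, and that 10% of the intervention arm and 2% of controls are abstinent.

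- Abstainers scored 0: 0.90 × 6 = 5.40 against 0.98 × 6 = 5.88, a difference of 0.48.
- Abstainers left out: 6 against 6, a difference of 0.

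A simulation in which the intervention acts only through abstinence gives a range. It assumes about 8 drinking days, a mean of 6 drinks per day (SD 2.5), and 5% of controls abstinent. The table shows the standardised difference.

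| Abstinent, intervention arm | Total | Ratio, abstainers left out | Ratio, abstainers scored 0 |
|---|---|---|---|
| 10% | 0.08 | 0.00 | 0.11 |
| 20% | 0.25 | 0.00 | 0.30 |

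None of these abstinence rates comes from the article.

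**The case against.** The best reply is that the body of the article agrees with itself. The Aims and Primary Outcomes both use drinks per drinking day, only the Abstract differs, and intensity per occasion is a legitimate target. The smallest correction would be to change the Abstract. That stands as a possible remedy, but it concedes that the text needs correcting.

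A second reply is that the trial would still see a fall in drinking days. In the 12-to-6 example every drinking day meets the threshold of 5 drinks, so binge frequency also falls from 12 to 6. That is true, but it is a secondary outcome and does not settle the primary comparison.

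Four stronger readings are tempting and are not supported:

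- *Abstainers will be treated as missing and modelled as if they still drank.* The Statistical Analysis section says only that missing data are handled by maximum likelihood. It does not say that a completed TLFB with no drinking days is coded missing. Scoring it 0 is equally compatible with the text, and such a rule could sit in an analysis plan that is not shown.
- *The sample size was built on the monthly total.* The cited effects concern the "for reduction in the number of drinks consumed [39,75"], which could be per month, per week or per drinking day.
- *Binge frequency is named as both primary and secondary.* The Aims place it under alcohol use without calling it primary, and Secondary Outcomes classes it clearly. The Aims are untidy, because their next sentence introduces the secondary outcomes separately, but this is not a second contradiction.
- *The definition will be picked to suit the result.* The article reports prospective registration, and the registered outcome cannot be seen here. The text leaves the choice open; it does not show any intent to use it.

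**Conclusion.** The contradiction between the Abstract and Primary Outcomes is real. An analysis plan could choose between the two, but as published the article gives two answers to what the primary alcohol-use outcome is. The consequence can be large for that one outcome: a 50% reduction on one definition can be no change on the other. How often this would happen in the trial cannot be derived from the article, because it depends on how far the intervention acts through frequency rather than quantity.

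The other two primary outcomes and the sample size are untouched. The zero-drinking-day issue is conditional: it matters only if the ratio is kept as primary and abstainers are left without a value. Its size in the illustrations rests wholly on assumed abstinence rates.

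**What to change.** Before analysis, name one variable as the single primary alcohol-use outcome at 8 weeks, in the same words in the Abstract, Aims and Primary Outcomes, and list the other as secondary.

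The past-month TLFB total, with abstainers scored 0, is the better choice. It has a value for every randomised participant who completes the assessment, and it reflects both how often and how much people drink. If drinks per drinking day is kept as primary, state the value given to a participant with no drinking days (for example 0), since those participants would drop out of the comparison if the ratio were left undefined.

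In the Aims, say that binge frequency is secondary, as the Secondary Outcomes section already has it.

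The cost is a few sentences. All three measures come from TLFB data already scheduled at every assessment, and neither the data collection nor the sample size changes.

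### The primary alcohol-consumption outcome is total past-month drinks in the Abstract but drinks per drinking day in the Methods, and nothing reconciles the two

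*Protocol article*

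**What the plan says.** The protocol article describes the consumption outcome in five places.

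- **Abstract, Methods:** "Primary outcomes will be the total number of standard drinks consumed in the past month", collected by TLFB. The total is itself the outcome.
- **Primary Outcomes:** "Primary outcomes for alcohol are consumption per drinking day, calculated from the total number of Australian standard drinks". The outcome is a ratio, and the total is what it is computed from.
- **Aims:** the first hypothesis concerns "alcohol use, including drinks per drinking day and frequency of binge drinking". This is an open list of examples and does not say which is primary.
- **Secondary Outcomes:** "Frequency of binge drinking (past month consumption of ≥5 standard drinks on 1 occasion" is derived from the same TLFB data and placed among the secondary measures.
- **Sample Size:** the cited earlier effects are "between 0.68 and 0.99 for reduction in the number of drinks consumed", with no period or denominator given.

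The Statistical Analysis section commits to intention-to-treat, with every randomized participant analysed in the allocated group, and to handling missing data by maximum likelihood.

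**The concern.** Total drinks combines how often a person drinks with how much they drink on those days. Drinks per drinking day keeps only the second part. The Abstract cannot be read as shorthand for the Methods, because the Methods variable needs a denominator (drinking days) that the Abstract never mentions.

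The programme can plausibly act on both parts: the intervention section and Table 2 describe content on avoiding or reducing drinking and on keeping to limits. The two measures could therefore give different answers. Either could be defended from the published text as the primary outcome once results are known. Who contributes data could also differ, because a participant with no drinking days has a total of 0 but no defined ratio.

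**Working it through.** **1. The plan's own figure.** Sample Size states that "a sample size of 90 (45 each group) would be required to detect a moderate effect size of 0.50", "with power=0.8 and alpha=.05", with an intraclass correlation of .55. Taking alpha as two-sided (the text does not say) and averaging three assessments, the variance factor is (1 + 2 × 0.55)/3 = 0.70. Then n per arm = 2 × (1.960 + 0.842)² × 0.70 / 0.50² = 2 × 7.85 × 0.70 / 0.25 ≈ 44, or 88 in total. That is within 2 of the stated 90, so the figure reproduces. Because it is built on a standardised difference, it serves either consumption measure, and choosing between them does not change it.

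**2. How the measures relate.** Total drinks = drinking days × drinks per drinking day. The monthly patterns below are illustrative and are not taken from the documents.

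| Change in pattern | Total | Per drinking day |
|---|---|---|
| 4 days of 2 plus 4 days of 8, to 4 days of 8 | 40 to 32 (-20%) | 40/8 = 5 to 32/4 = 8 (+60%) |
| 12 days of 6, to 6 days of 8 | 72 to 48 (-33%) | 6 to 8 (+33%) |
| 12 days of 6, to 6 days of 6 | 72 to 36 (-50%) | 6 to 6 (0%) |

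In the first two rows the measures move in opposite directions. In the third, one halves and the other does not change.

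**3. Participants who stop drinking.** With no drinking days the total is 0 and the ratio is 0/0. If such a value is left undefined, the mixed model treats it as missing, although the participant responded and had the best possible consumption result. That does not fit the commitment to analyse all participants.

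**4. Cost of a free choice.** If both measures are tested at two-sided .05 and either may be called primary, the chance of at least one false positive is 1 − P(|Z1| ≤ 1.96 and |Z2| ≤ 1.96), with Z1 and Z2 bivariate normal. The correlation is not in the documents, so a range is shown.

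| Assumed correlation | At least one significant | At least one significant in one given direction |
|---|---|---|
| 0 | .0975 | .049 |
| .5 | .091 | .045 |
| .7 | .083 | .042 |
| .9 | .070 | .035 |

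The nominal values are .05 and .025. Both measures come from the same diary, so .5 to .9 is the more plausible part of the range, which gives about .09 to .07.

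**5. Power, as illustration only.** A simulation assumed 39 observed per arm (122 × 0.65 / 2 ≈ 39.7), 30 days, a mean drinking-day probability of .3 and a median of 5.5 drinks on a drinking day. Between-person spread and stability over time were varied. With 40% fewer drinking days, power on the total ranged from 55% to 97%; the ratio stays at about the 5% error rate, because frequency and intensity were set independent. With 25% lower intensity, power was 23% to 67% on the total and 40% to 94% on the ratio. Only the ordering should be relied on: each measure does better for a different kind of effect.

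**The case against.** The strongest reply is that the detailed Methods text should override a condensed abstract, that the two measures usually move together, and that the trial was prospectively registered. Part of this stands. The measures are probably correlated, so a conflict is a possibility and not a forecast. But the article nowhere says that one section takes precedence, and the registry content is not shown, so it neither cures nor worsens the contradiction.

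A reader might also infer more than the document supports:

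- **That the Aims confirm drinks per drinking day as primary.** They give examples of alcohol use and name no primary outcome. One of those examples, binge frequency, is secondary elsewhere. The contradiction lies between the Abstract and Primary Outcomes.
- **That under the Methods definition a fall in drinking days would go unseen.** Only this one variable would miss it. The alcohol-harm questionnaire is also primary, binge frequency counts occasions, and Table 1 repeats the Alcohol Use Disorders Identification Test at both follow-ups. Any of these could register the change.
- **That the sample size was planned on the wrong measure.** The cited effects are described only as concerning the number of drinks. Whether the source trials counted per month, week or occasion cannot be told from this document. The planning value of 0.50 lies below all the cited effects.
- **That total drinks is the only correct choice.** The ratio is the better measure for a pure intensity effect, and drinking limits are a stated target of the programme. The choice is a trade-off for the investigators.

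**Conclusion.** The concern holds as an internal contradiction: one of three primary outcomes has two definitions, in the Abstract and in Primary Outcomes. This is conflicting stated content, not detail that an article leaves to a fuller plan. That the measures can diverge, and that the ratio fails for abstainers, follows from arithmetic and needs no assumption about the data. The error inflation, from .05 to about .07 to .09, is conditional: it assumes a correlation of .9 to .5 and that the more favourable result would be reported. It does not follow that the alcohol result will be won or lost on this point, because the measures may well agree. The sample size of 90 is unaffected. The point should still be settled before unblinded analysis, since afterwards neither choice could be shown to be independent of the results.

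**What to change.** Before unblinded analysis, name one TLFB consumption measure as the primary outcome, use it in the Abstract, Aims and Primary Outcomes, and list the other as secondary.

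- **If total past-month drinks is chosen:** it matches the Abstract, captures both frequency and intensity, and is defined for abstainers. The price is a more skewed variable and less power for an effect on intensity alone. Primary Outcomes and the Aims need rewording.
- **If drinks per drinking day is kept:** correct the Abstract and state that participants with no drinking days in the month are scored 0, so that all participants can be analysed.

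Either way the cost is wording only. The same TLFB data yield both measures, so no assessment or sample-size figure changes.
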